### Sample size

Sample size was calculated based on the literature change of HAMD-24 scores as a primary outcome measure, using the following formula for a comparison between the two groups:

$$n_{2}=\frac{k+1}{k}\frac{{\left(Z_{\alpha /2}+Z_{\beta }\right)}^{2}\sigma^{2}}{\delta^{2}}$$

$$n_{1}=kn_{2}$$

A two-sample *t* test was selected in this research; σ represents the difference between the standard deviations of the HAMD-24 scores at 4 weeks in the experimental group (EA + rTMS) and the control group (rTMS) and δ indicates the difference between the means of the HAMD-24 scores in the two groups. G·Power software (version 3.1.9.7) was used for sample size calculation. According to the results from existing published literature (29), the mean (standard deviation) of the HAMD-24 at baseline before treatment was 27.52 (2.06) for the experimental group and 27.84 (2.55) for the control group. The mean (standard deviation) of the HAMD-24 after 4 weeks of treatment was 11.06 (3.37) for the experimental group and 14.13 (3.15) for the control group. To achieve a power (1 − β) of 0.90 at an alpha level of 5% (2-tailed) and a k value of 1, it was estimated that approximately 25 individuals will be needed in each group. Anticipating a 20% drop-out rate, a total of 64 subjects will be recruited to take part in the study, with 32 patients in each group. Moreover, 10 healthy subjects will be involved in the study, from which normal MRI data will be collected, without randomization and intervention.

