### Statistical analysis

All data analyses of this study will be done by an independent statistician ([name]) from University of Cape Town in South Africa using IBM SPSS Statistics for Windows, version 25.0 (IBMCorp., Armonk, N.Y., USA). The modified intention to treat (mITT) principle will be applied for all outcomes in the full analysis set. If the endpoints are missing, the last-observation-carried-forward (LOCF) method will be used according to mITT analysis. The mean, standard deviation (SD), minimum (min), maximum (max), and median will be reported for the quantitation data. The frequency (*n*) and corresponding percentage (%) will be given for the enumeration data. For intra-group comparisons, Student’s paired t test or Wilcoxon signed rank test will be used, and the chi-squared test will be utilized for qualitative indexes. For inter-group comparisons, independent-sample T test or Mann–Whitney U test will be applied. Pearson correlation coefficient or Spearman correlation coefficient will be used for correlation analysis between scale scores and fMRI data. An alpha level of 5% (2-tailed) will be selected.

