## Discussion

PSD, a typical neuropsychiatric disorder, is lacking in long-term safe and effective treatments. Therefore, except for antidepressants, it is necessary to find other non-pharmaceutical anti-depression alternatives with safe and effective performance and explore its mechanisms.

In recent years, EA and rTMS have been the most popular alternative therapies for depression and are increasingly used all over the world. A recent randomized controlled trial showed that EA is an efficacious and safe treatment to alleviate the depressive symptoms of PSD and improve neurological function regarding ADLs among stroke patients (30). A new meta-analysis demonstrated that rTMS for PSD also has a positive impact on depression and ADLs compared to antidepressants without any obvious adverse reactions (15). However, few studies were conducted on EA combined with rTMS for the treatment of PSD, and rTMS trials rarely consider individual anatomical MRI-guided neuronavigation.

Depression is the most frequent psychiatric symptom after stroke. Its pathogenesis is associated with lesion of the brain structure and function caused by stroke (31). fMRI studies have revealed that PSD patients tend to be marked by reduced mutual inhibition between functional circuits involving the DMN and nucleus accumbens, as well as volumetric and microstructural changes within these networks (32). It has been found that improvements in depressive symptoms following rTMS are relevant to functional alterations of different brain areas within the DMN of PSD patients (33). The DMN includes the bilateral precuneus, medial prefrontal lobe, anterior cingulate, posterior cingulate gyrus, and inferior parietal lobule, which is mainly responsible for self-consciousness regulation and emotional processing (34). We assume that the psychopathological network for depressive emotion processing deficit in PSD may mainly be associated with the DMN. Existing studies on EA for treating PSD are mostly focused on clinical depressive performance with scales but not brain responses to EA based on fMRI. Hence, a randomized, controlled, open-label trial is designed to explore the efficacy and neuromechanism of EA and MRI-navigated rTMS on PSD. Moreover, we will examine the change of the DMN and how this reflects the emotional function as a special brain network regulator, using ICA measures to provide reliable clinical markers for PSD.

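### The brain–mood correlation is an unadjusted pairing of scale scores with fMRI data; if arms are pooled, it can be significant with no association within either arm

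*Protocol article*

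**What the plan says.** Protocol article, Statistical analysis: a Pearson or "Spearman correlation coefficient will be used for correlation analysis between scale scores and fMRI data". The same section adds "An alpha level of 5% (2-tailed) will be selected". It gives paired tests within groups, independent-sample tests between groups, and last observation carried forward (LOCF) for missing endpoints under mITT.

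Protocol article, Discussion, on the aim: "we will examine the change of the DMN and how this reflects the emotional function". The sentence goes on to name ICA as the measurement tool and reliable clinical markers as the goal.

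Protocol article, Outcome measures: the first primary outcome is change in HAMD-24 and the second is change in rs-fMRI. Both are measured at baseline and at 4 weeks.

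Protocol article, Sample size: the assumed week-4 HAMD-24 means (SD) are "11.06 (3.37) for the experimental group and 14.13 (3.15) for the control group", and "approximately 25 individuals will be needed in each group". Recruitment is 32 per arm after allowing for 20% drop-out.

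**The concern.** The paired and between-group tests show whether each measure moves. Only the correlation sentence says whether brain and mood move together, so that link depends on how the sentence is carried out.

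A plain two-variable coefficient tests for no association from any source, including treatment arm. The trial is sized for a large arm difference in HAMD-24 and hopes to find an fMRI difference too. If both appear and the arms are pooled, the two group means alone produce a correlation, even if no patient's fMRI value tracks that patient's mood. It could then be reported as a neural correlate or clinical marker when it only restates two arm differences. The sentence also refers to scores, while both primary outcomes are defined as change.

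**Working it through.** **Inputs from the Sample size section.** HAMD-24 at baseline: "27.52 (2.06) for the experimental group and 27.84 (2.55) for the control group". At week 4: "11.06 (3.37) for the experimental group and 14.13 (3.15) for the control group". Design: power "of 0.90 at an alpha level of 5% (2-tailed) and a k value of 1".

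**The plan's own figure.**
- Difference: 14.13 − 11.06 = 3.07.
- Pooled SD: √((3.37² + 3.15²)/2) = 3.26.
- d = 3.07/3.26 = 0.94.
- The normal approximation gives 24 per arm. The noncentral t calculation gives 25 per arm, with power 0.903.
- 25/0.80 = 31.25, rounded up to 32 per arm, 64 in total.

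The sample size reproduces. No figure is stated for the correlation.

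**Correlation induced by pooling arms.** With equal arms, zero association within arms, and arm differences d_H (HAMD-24) and d_F (fMRI) in SD units, the size of the pooled correlation is

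r = (d_H/2)(d_F/2) / √[(1 + d_H²/4)(1 + d_F²/4)].

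With d_H = 0.94:
- d_F = 0.2: 0.47 × 0.10 / √(1.2209 × 1.01) = 0.04
- d_F = 0.5: 0.47 × 0.25 / √(1.2209 × 1.0625) = 0.10
- d_F = 0.8: 0.47 × 0.40 / √(1.2209 × 1.16) = 0.16

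**Rejection rates.** Simulation with 20,000 trials per setting, week-4 HAMD-24 drawn from the means and SDs above, fMRI independent of it within each arm, two-sided 5% Pearson test. The d_F values are assumptions, because the article gives none.

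| Assumed fMRI arm difference | 25 per arm, pooled | 32 per arm, pooled | Arm-adjusted |
|---|---|---|---|
| 0 | 5% | 5% | about 5% |
| 0.2 SD | 6% | 6% | about 5% |
| 0.5 SD | 11% | 13% | about 5% |
| 0.8 SD | 20% | 24% | about 5% |

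Spearman agrees within 1 point. If the fMRI measure differs by 0.8 SD but HAMD-24 does not differ, the rate is 5.3%: both variables must shift.

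**Other readings of the sentence.**
- *Change scores, arms pooled, no adjustment, 64 patients:* 10–17% at an fMRI arm difference of 0.5 SD and 16–32% at 0.8 SD, for an assumed baseline-to-week-4 HAMD-24 correlation of 0 to 0.7. Change scores alone do not solve the problem. If the fMRI shift over time is the same in both arms, the rate is about 5%.
- *Both visits stacked:* mean HAMD-24 falls from (27.52 + 27.84)/2 = 27.7 to (11.06 + 14.13)/2 = 12.6. With an assumed fMRI visit shift of 0.2 SD the rate is 9–15% (50 patients) or 12–18% (64). At 0.5 SD it is 63–66% or 74–79%.
- *Each arm separately:* about 5%, so valid. Power for an assumed true r = 0.35 by Fisher's z, atanh(0.35) = 0.365: 0.365√22 − 1.96 gives 40% at n = 25, and 0.365√29 − 1.96 gives 50% at n = 32. Using both arms with arm adjustment, √46 and √60 give 70% and 81%.

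**Does the LOCF rule affect the remedy?** Under LOCF a drop-out has zero change on both variables, while completers' HAMD-24 falls by 27.52 − 11.06 = 16.46 or 27.84 − 14.13 = 13.71. The drop-outs form a cluster at the origin. With 32 per arm, 20% carried forward, no true association and an assumed HAMD-24 visit correlation of 0.5, even the arm-adjusted change correlation rejects about 7%, 29% and 77% of the time at assumed common fMRI changes of 0.3, 0.5 and 0.8 SD. Restricted to patients observed at both visits, it rejects about 5%.

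**The case against.** The strongest reply is that the fault is read into one supporting sentence. A condensed article may leave the choice of scores, visits and arms to a fuller document. Both primary outcomes are defined as change, so stacking visits is the least natural reading, and analysing each arm separately would be valid. This stands: the article neither prescribes nor rules out pooling. What remains is that the method it does name carries no arm adjustment and is expressed in scores, which does not fit the stated aim.

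Two stronger readings are tempting and are not supported. A reader might infer that any arm or visit shift invalidates the test. It does not: both variables must shift across the same pooled factor, and an equal visit shift cancels in change scores. A reader might also infer that the whole mechanism claim rests on this correlation. The Abstract and Outcome measures make rs-fMRI change itself the main mechanism outcome, tested separately.

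It can also be said that a marginal correlation is a legitimate description, since arm adjustment removes covariation that treatment produces. That is fair, provided it is not presented as showing that patients' brain and mood measures move together within arms. Finally, the Discussion speaks of DMN change and emotional function, not explicitly of change in emotional function, and it names ICA. But ICA extracts the network; it does not relate it to HAMD-24.

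The power comparison also depends on the assumed r: at r = 0.5 the same formula gives 73% to 84% per arm.

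**Conclusion.** The point holds conditionally and is minor. The only stated brain–mood analysis is unadjusted and does not match the aim of relating DMN change to emotional function. If arms are pooled and both variables differ by arm, the nominal 5% error becomes about 11–13% at a 0.5 SD fMRI arm difference and 20–25% at 0.8 SD, for 25 to 32 per arm. At 0.2 SD it is about 6%, which is negligible.

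The HAMD-24 difference comes from the article; every fMRI shift is assumed. Stacking visits would be worse, but the text does not prescribe it. Separate per-arm correlations are valid but less powerful. Neither the sample size nor the HAMD-24 comparison is affected.

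**What to change.** Replace the correlation sentence with text to this effect: the association between change in HAMD-24 and change in each fMRI measure (week 4 minus baseline) will be estimated by partial correlation, Pearson or rank-based, adjusted for treatment arm, with a 95% CI, in patients with both measures observed at both visits. LOCF values will not be used in this analysis, and neither stacked visits nor healthy subjects will be pooled into it. By-arm estimates will be shown descriptively.

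All three elements are needed. Change scores match the aim, arm adjustment removes the group-mean artefact, and restriction to observed pairs avoids the cluster of zero changes. Healthy subjects should stay out because the inclusion criteria separate them from patients on HAMD-24 (below 8 against above 8), which would build in another group shift.

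The cost is one degree of freedom, the assumption of a common slope in both arms, and the loss of imputed pairs. At the planned 20% drop-out that leaves about 50 patients, with power of about 70% for an assumed r = 0.35. No new data are needed.

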### Quality control

With the aim to enhance the feasibility and safety of intervention, one EA therapist ([name]) and one rTMS therapist ([name]) with 5 years of experience will be the fixed personnel for the patients, and the MRI scan technician ([name]) and outcome evaluator ([name]) will probably the same as in the authorization table. Before the study starts, all involved researchers will take several training courses to understand the study protocol, MRI scanning, scales assessment, and the research process. Patient compliance will be a vital factor in the trial. Hence, the following will be conducted throughout the entire study. Firstly, therapists will strictly comply with the informed principle and will assist patients in learning the potential benefits and harms. Secondly, the patients will be required to truthfully complete treatment cards after every treatment. Thirdly, therapists will be able to contact patients using WeChat and phone to provide a kind reminder of the following visit 2 days in advance. In addition, the PI and CRA will strictly carry out three-level quality control management every week, 2 weeks, and 4 weeks throughout the study. The CRA will regularly check the pCRF and eCRF. Traces of modifications will remain. After data entry and verification, the PI will lock the ResMan database for final data analysis, which will be performed by our partner, a professional neuroimaging expert ([name]) from the University of Cape Town, South Africa. The abovementioned measures, to a large extent, will ensure the reliability and repeatability of the research results.

### Trial status

The current study protocol version is 1.0 as of 9 June 2022. After clinical registration, recruitment and randomization began on 22 October 2022. This trial is projected to end on schedule in August 2025.

## Discussion

PSD, a typical neuropsychiatric disorder, is lacking in long-term safe and effective treatments. Therefore, except for antidepressants, it is necessary to find other non-pharmaceutical anti-depression alternatives with safe and effective performance and explore its mechanisms.

In recent years, EA and rTMS have been the most popular alternative therapies for depression and are increasingly used all over the world. A recent randomized controlled trial showed that EA is an efficacious and safe treatment to alleviate the depressive symptoms of PSD and improve neurological function regarding ADLs among stroke patients (30). A new meta-analysis demonstrated that rTMS for PSD also has a positive impact on depression and ADLs compared to antidepressants without any obvious adverse reactions (15). However, few studies were conducted on EA combined with rTMS for the treatment of PSD, and rTMS trials rarely consider individual anatomical MRI-guided neuronavigation.

Depression is the most frequent psychiatric symptom after stroke. Its pathogenesis is associated with lesion of the brain structure and function caused by stroke (31). fMRI studies have revealed that PSD patients tend to be marked by reduced mutual inhibition between functional circuits involving the DMN and nucleus accumbens, as well as volumetric and microstructural changes within these networks (32). It has been found that improvements in depressive symptoms following rTMS are relevant to functional alterations of different brain areas within the DMN of PSD patients (33). The DMN includes the bilateral precuneus, medial prefrontal lobe, anterior cingulate, posterior cingulate gyrus, and inferior parietal lobule, which is mainly responsible for self-consciousness regulation and emotional processing (34). We assume that the psychopathological network for depressive emotion processing deficit in PSD may mainly be associated with the DMN. Existing studies on EA for treating PSD are mostly focused on clinical depressive performance with scales but not brain responses to EA based on fMRI. Hence, a randomized, controlled, open-label trial is designed to explore the efficacy and neuromechanism of EA and MRI-navigated rTMS on PSD. Moreover, we will examine the change of the DMN and how this reflects the emotional function as a special brain network regulator, using ICA measures to provide reliable clinical markers for PSD.

This study does have several limitations. Firstly, it fails to blind patients due to the particularity of EA and rTMS, which may cause performance bias. Secondly, because of limited research grants, the study period only includes the treatment period, without the follow-up period, which makes it impossible to evaluate the long-term efficacy. Moreover, the rs-fMRI results may be influenced by different brain regions of cerebral infarction. The relationship between different infarcts and depression symptoms should be investigated in future studies.

In conclusion, this protocol is strictly reported following the requirements of the SPIRIT statement and the corresponding extension. The results generated from this rigorous design will have high reliability and provide clinical evidence for the underlying benefits and neural correlates of EA and MRI-navigated rTMS for PSD.

## Ethics statement

The studies involving humans were approved by Ethics Committee of the Affiliated Drum Tower Hospital, Medical School of Nanjing University. The studies were conducted in accordance with the local legislation and institutional requirements. The participants provided their written informed consent to participate in this study.

## Glossary

ADL: Activity of daily living
AE: Adverse event
ALFF: Amplitude of low frequency fluctuations
BOLD: Blood oxygen level dependent
CRA: Clinical research associates
CRF: Case report form
DLPFC: Dorso-lateral prefrontal cortex
DMN: Default mode network
EQ-5D: EuroQol Five Dimensions Questionnaire
fMRI: Functional magnetic resonance imaging
FC: Functional connectivity
GCS: Glasgow coma scale
HAMD: Hamilton Depression Rating Scale
HSTCM: Health Scale of TCM
ICA: Independent component analysis
KCC: Kendall’s coefficient concordance
MBI: Modified Barthel index
MEP: Motor evoked potential test
mITT: Modified intention to treat
NIHSS: National Institutes of Health Stroke Scale
PI: Principal investigator
PSD: Post-stroke depression
ReHo: Regional homogeneity
rMT: Resting motor threshold
rTMS: Repetitive transcranial magnetic stimulation
